##### Shoulder Function and Range of Motion

Upper-body function is assessed using the Y Balance Test Kit (Move2Perform) [61]. Participants begin in a 3-point plank position on the toes or knees depending on ability. The tested shoulder is the supporting limb placed on the connecting block, the nontesting limb is placed on the medial block, and the feet are placed shoulder-width apart. From this position, the participant uses their nontesting limb to move each reach block one at a time in the medial, inferolateral, and superolateral directions in a controlled manner as far as they can and then return to the starting position. The test is performed 3 times on each side with a 30-second rest between trials. The reach distance in each direction is recorded, where the highest value in each direction is used to calculate an average composite score.

Bilateral upper-body strength and power are assessed through the seated medicine ball throw [62]. Participants are instructed to sit on the floor with their head, shoulders, and back against the wall and legs extended; legs may be bent if ability does not allow for full extension. To calculate a relative throwing distance, arm-reach distance is measured from the wall in meters. Using a 2-kg medicine ball covered in chalk, the participant performs a chest pass holding the ball with both hands and throwing it forward in a straight line as far as they can with head, shoulders, and back maintaining full contact with the wall. A measuring tape is used to measure the distance from the wall to the most proximal point of the chalk mark, with the participant’s reach distance subtracted to provide a final distance in meters. In total, 3 test trials will take place after a practice throw with a 1-minute rest between each trial. The average of the 3 trials will be calculated.

Shoulder function is assessed through the shoulder performance test using the following tasks: overhead reach, hand behind the head, and hand behind the back. All movements are completed in a standing position starting with the arms by the side. The time (seconds) taken to complete the respective tasks using the correct technique 20 times is recorded. Each task is repeated to the right and left.

Upper-body function is assessed using the closed kinetic chain upper-extremity stability test [63]. Participants begin in a 3-point plank position on the toes or knees, depending on ability, with hands 36 inches (91.4 cm) apart, shoulders perpendicular to hands, and feet hip-width apart. From this position, the dominant hand reaches across the body, touches the nondominant hand, and returns to the starting position. Subsequently, the same movement is performed by the nondominant hand. Participants are instructed to perform as many alternating touches as possible in 15 seconds while maintaining the correct push-up position. In total, 3 trials occur after familiarization, with 45 seconds of rest in between each trial.

Shoulder active range of motion (AROM) is measured on both upper limbs. Using a goniometer (EZ Read; Jamar), AROM is assessed in external rotation at 0°, external rotation at 90°, forward flexion, and abduction [64,65]. The participant stands for all tests except for external rotation at 90°, where the participant is lying on the ground with knees bent and feet hip-width apart. The starting position of the measured limb is dictated by the AROM being tested. The participant is asked to actively perform the required motion with the angle of movement recorded in degrees. In total, 3 active trials are performed after the tester passively moves the participant’s limb in the tested motion.

##### Physical Activity and Sedentary Behavior

Physical activity and sedentary behavior are assessed using the ActiGraph wGT3X-BT (ActiGraph LLC) at baseline, after the intervention, and at follow-up only. Patients wear the accelerometer on their hip for 7 consecutive days, excluding water-based activities and sleep. ActiLife software (ActiLife 6; ActiGraph LLC) is used to analyze the ActiGraph data. Only wake wear time is used, with a minimal data collection period set for inclusion in the analysis of 4 days of at least 600 minutes per day. Nonwear time is excluded from the analysis, defined as ≥90 minutes of consecutive zeros with a 2-minute spike tolerance [66]. Commonly used cutoff points among patients with cancer will be used to classify sedentary time (<100 counts per minute), light physical activity (100-1951 counts per minute), and moderate to vigorous physical activity (≥1952 counts per minute) [67-69].

#### Covariates

##### Participant Characteristics

Participant demographic and medical history data are collected at baseline with the administration of a study-tailored questionnaire. In addition, patients complete the Socioeconomic Status Questionnaire to determine economic demographics, education level, and socioeconomic status [70]. Changes in demographic and medical history data (eg, medical conditions, medication, and cancer treatment) will be monitored throughout the study period and confirmed at each testing time point.

##### Dietary Intake

Recent dietary patterns are assessed using the automated self-administered 24-hour dietary assessment tool [71]. Participants complete 3 assessments at home on 2 weekdays and 1 weekend day, recording all food and drinks consumed during the previous 24-hour period.

##### Physical Activity Logs

The AC group completes a daily activity log throughout the 16-week intervention. During the supervised exercise sessions, the HIIT group is asked about their physical activity completed outside the supervised sessions over the previous week. In addition, they complete daily activity logs during the follow-up period. In the activity logs, the participants are asked to record the type of exercise performed, the time spent performing the exercise, the intensity of the exercise bout (rate of perceived exertion [Borg scale 1-10] or average HR for the HIIT group if they are wearing an HR monitor), and the day of the week in which it was completed.

### Intervention

#### HIIT Group

Participants randomized to this group partake in a clinic-based HIIT program using a cycle ergometer 3 days per week for 16 weeks under the supervision of a trained exercise oncology specialist. Before beginning the exercise session, participants undergo a screening procedure to ensure that they are fit to participate. Participants are permitted to participate in the exercise session if they present with normal body temperature (≤100 °F or ≤37.8 °C), resting HR (absence of bradycardia, <60 beats per minute; or tachycardia, >100 beats per minute), and resting blood pressure (≤200/120 mm Hg). In addition, participants complete the Exercise-Induced Feeling Inventory [72] before and after the HIIT session to assess the participants’ feeling state changes after exercise and self-motivation to adhere to an aerobic exercise regimen. Participants also complete the Therapy-Related Symptom Checklist [73], a 25-item questionnaire, to assess and identify patient-reported symptom occurrence and severity.

The cycle-based HIIT exercise session consists of a 5-minute warm-up period at 10% of POmax (watts; calculated from the cardiopulmonary exercise test) followed by a 20-minute stimulus period consisting of alternating high-intensity interval bouts at 90% POmax (based on individual fitness level) with a recovery bout at 10% at a 1 minute:1 minute (work:recovery) ratio (Figure 2). Following the stimulus period, participants complete a 5-minute cooldown at 10% POmax (watts). An HR monitor wristwatch and transmitter are used to measure HR before exercise and at every minute during warm-up, exercise, and cooldown. Exercise sessions are completed with at least one full day of rest in between each session and are not to be completed on days when the participant has a chemotherapy infusion. Weekly goals will be set by the study staff for each participant based on their symptoms and how they feel overall, allowing for tailored sessions to accommodate individual fitness ability and treatment burden.

**Figure 2 figure2:**
[figure not shown]
Example of a high-intensity interval training session and the high and low intensities performed.

Exercise intensity is gradually increased within the first 4 weeks of the intervention, whereby the participants begin the high-intensity interval bouts at 60% POmax, increase by 10% each week until 90% is reached, and then maintain at 90% for the remainder of the intervention (Figure 3). If a participant is unable to achieve compliance with the prescribed HIIT program, a moderate-intensity interval training (MIIT) program is substituted as an alternative exercise prescription. A single session is considered noncompliant if the number of high-intensity bouts achieving the target power output is <80% (eg, if ≥3 high-intensity bouts do not reach the prescribed power output). If 3 concurrent exercise sessions are reported as noncompliant, the participant is offered the MIIT program instead. Within the MIIT program, participants continue to complete intervals at a 1 minute:1 minute (work:recovery) ratio; however, the high-intensity bout is replaced with a moderate-intensity power output target. The intensity of the moderate interval is calculated as a percentage of the individual’s estimated VO_2max_ and will be selected according to the highest intensity that the participant may tolerate or complete. After the aerobic exercise session, the participants will perform 1 set of 3 to 4 static stretching exercises held for 30 seconds.

**Figure 3 figure3:**
[figure not shown]
High-intensity bout progression over the course of the 16-week high-intensity interval training intervention.

#### AC Group

Participants randomized to this group perform a home-based flexibility intervention 3 days per week for 16 weeks. The stretching protocol consists of the same stretching exercises as in the HIIT program. As flexibility exercises are low-intensity, low-impact, and low-volume, minimal caloric expenditure is expected. To increase compliance [74] and aid in the standardization of the home-based stretching [75], participants are provided with an instructional booklet of the flexibility exercises. Participants are asked to enter these stretching bouts into the daily activity log in addition to the other self-directed exercise sessions performed. Participants in the AC group are offered to participate in the same experimental exercise condition (HIIT) after the first 16-week study period; if they do not choose to participate in the HIIT program, they are not required to complete follow-up testing and are finished with the study after the first 16 weeks. The AC participants who choose to take part in the HIIT protocol after the initial 16 weeks return at the follow-up testing time point for final testing, which serves as post-HIIT testing.

#### Intervention Adherence

Participant adherence to the HIIT program is measured using (1) percentage and number of prescribed sessions attended (participants must attend ≥80% of the 48 sessions to be considered compliant with the HIIT program; eg, ≥38 sessions) and (2) average minutes of exercise per week (participants must complete ≥80% of the prescribed 90 minutes per week; eg, ≥72 minutes per week). To support adherence throughout the intervention, flexible hours are offered for exercise sessions, including before or after normal working hours and on weekends. In addition, all participants are given an additional 2 weeks beyond the 16-week intervention period to make up for any exercise sessions missed because of illness, work, or travel. Participants are provided with monetary compensation for each MRI completed and parking validation for every visit to the Dana-Farber Cancer Institute.

### Adverse Events

Any expected and unexpected adverse events are or will be reported to the principal investigator, who then subsequently reports to the institutional review board of the Dana-Farber Cancer Institute. Serious events must be reported within 24 hours of occurrence or finding out about the event. All adverse events, both serious and nonserious, and deaths that are encountered from the initiation of the study intervention, throughout the study, and within 30 days of the last study intervention are followed to their resolution or until the principal investigator assesses them as stable or determines the event to be irreversible or the participant is lost to follow-up. The presence and resolution of adverse events are documented on the appropriate case report form and recorded in the participant’s medical record.

### Data Monitoring and Management

Data are monitored internally within the Dana-Farber Cancer Institute for timeliness of submission, completeness, and adherence to protocol requirements. Monitoring begins at the time of participant registration and will continue during protocol performance and completion. The study team collects, manages, and performs quality checks of the data. Potential audits or inspections may be conducted by the principal investigator or their designated representatives. All data are stored on a secure network drive using REDCap (Research Electronic Data Capture; Vanderbilt University), a Health Insurance Portability and Accountability Act–compliant web-based application hosted by Partners HealthCare Research Computing, Enterprise Research Infrastructure & Services, on password-protected computers. Any hard-copy data are stored in locked filing cabinets in card-access facilities. The results of this study will be presented in publication, conference, and invited speaker formats.

### Sample Size Calculation

We will enroll 50 patients with breast cancer (n=25, 50% per group) in this study. We estimate that the dropout rate will at most be 20%. Assuming a 20% dropout, data from 40 (n=20, 50% per group) patients will be available for the analyses. With this sample size, we will be able to estimate within-group means for our outcome variables with a 95% CI of –0.47 to +0.47 SD units and mean differences between groups with a 95% CI of –0.64 to +0.64 SD units. Although the primary objective of the analysis for this pilot study is not to detect a between-group difference but to estimate the effect size for designing a subsequent confirmatory study, we also calculated a detectable effect size for the between-group comparison for reference. This sample size offers 80% power to detect a between-group difference at a .05 2-sided *α* level when the difference is 0.91 SD units.

### Statistical Analysis

Analyses will reflect the trial hypotheses that involve comparisons of HIIT and AC. Initial descriptive analyses will evaluate baseline comparability between the 2 intervention groups using the 2-sample, 2-tailed *t* test or 2-sample Wilcoxon test for continuous variables and the chi-square test or Fisher exact test for categorical variables. The primary analysis variables will be changed from baseline to week 16 of neuroimaging and cognitive function measures. Summary statistics (mean, SD, median, IQR, minimum, and maximum) will be used to describe the distribution of the variables. The mean and median will be reported along with the corresponding 95% CIs. Paired tests will be performed for these continuous outcomes for each group to assess whether there is a significant difference between baseline and week 16 in each group. For between-group comparison, a 2-sample *t* test will be performed. Analysis of covariance will also be used to assess the intervention effect on those continuous outcomes (changes from baseline to week 16), adjusting for patient baseline characteristics and other clinical covariates, including any participant who is required to switch to MIIT. Furthermore, those who are transferred to the MIIT group will be included in the HIIT group in the primary analysis based on the intention-to-treat principle. As an exploratory analysis, we will identify baseline factors of the patients who are likely to be transferred to the MIIT group. We will then exclude those who are transferred to the MIIT group and compare the HIIT and AC groups adjusting for factors that affect the transfer from HIIT to MIIT. Chi-square tests will be used for group comparison of binary outcomes (eg, the occurrence of adverse events). The magnitude of the intervention effect on binary outcomes will be summarized using odds ratio and the corresponding 95% CI. For each analysis, a 2-sided *P* value of <.05 will be considered statistically significant. As this is a pilot study, we will not adjust for multiple testing. Linear mixed-effects models will be used to estimate the trajectories of those repeatedly measured continuous outcomes across the intervention to assess group differences and explore the impact of potential prognostic factors (eg, body weight, age, fat mass, race, and menopausal status) on outcomes. Linear mixed-effects models will also be used for exploratory analysis of potential neuroimaging biomarkers. The primary analysis will include all completed outcome assessments (regardless of whether the woman stayed on the intervention), inviting those who drop out of the intervention to return for outcome assessments. The only missing data would be of those who drop out of the intervention and do not return for outcome assessments. Preliminary analyses will compare women who do and do not contribute to this analysis of baseline characteristics. A sensitivity analysis will include multiple imputations of all missing outcome data, including those patients who have missing assessments.

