**Conclusions:**

This first-of-its-kind study incorporates a novel exercise intervention (ie, HIIT) and comprehensive cognitive measures. If positive, our findings will establish the pilot efficacy of HIIT on chemotherapy-induced cognitive function in patients with breast cancer, providing the foundation for future larger phase-II and phase-III trials to confirm the findings and potentially establish HIIT as a standard of care for women undergoing chemotherapy for breast cancer.

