### Objectives

The primary aim of the Improving Cognitive Function Through High-Intensity Interval Training in Breast Cancer Patients Undergoing Chemotherapy (CLARITY) trial is to examine the impact of a 16-week HIIT exercise intervention on cognitive function assessed using the Montreal Cognitive Assessment, the National Institutes of Health (NIH) toolbox, and quantitative magnetic resonance imaging (MRI) of the brain. We hypothesize that executive function and memory scores will be higher after exercise compared with baseline and the attention control (AC) group and that participants in the HIIT intervention will have enhanced functional brain connectivity and structural white matter tracts compared with baseline and the AC group. The secondary aims are to examine the effects of HIIT on body composition; biomarkers related to metabolic dysregulation, inflammation, and cardiotoxicity; physical fitness and function; and quality of life and psychosocial outcomes in patients diagnosed with early-stage breast cancer undergoing chemotherapy. We hypothesize that participants in the HIIT intervention will have improved body composition and psychosocial health compared with baseline and the AC group.

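### Within-arm paired significance tests and a hypothesis of change from baseline cannot show a HIIT effect, and the efficacy wording does not fit a pilot that aims to estimate

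*Protocol article*

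**What the plan says.** - **Hypothesis (Objectives).** The article expects that "executive function and memory scores will be higher after exercise compared with baseline and the attention control (AC) group". The imaging hypothesis has the same two comparators.
- **Within-arm tests (Statistical Analysis).** "Paired tests will be performed for these continuous outcomes for each group to assess whether there is a significant difference between baseline and week 16". These apply to the primary analysis variables, which are the changes in neuroimaging and cognitive measures.
- **Between-arm test (same section).** "For between-group comparison, a 2-sample *t* test will be performed", with analysis of covariance in addition.
- **Threshold and multiplicity (same section).** "For each analysis, a 2-sided *P* value of <.05 will be considered statistically significant", and "As this is a pilot study, we will not adjust for multiple testing".
- **Aim (Sample Size Calculation).** The purpose is "not to detect a between-group difference but to estimate the effect size for designing a subsequent confirmatory study". Power is given for reference only.
- **Claim (Abstract, Conclusions).** "If positive, our findings will establish the pilot efficacy of HIIT on chemotherapy-induced cognitive function in patients with breast cancer". The Conclusions at the end of the Discussion repeat the efficacy claim without the condition.

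The primary outcomes are not the same list everywhere:

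| Section | Cognitive | Imaging |
|---|---|---|
| Abstract, Methods | Executive function and memory by NIH toolbox | Resting-state connectivity, DTI microstructure |
| Objectives | NIH toolbox and Montreal Cognitive Assessment | Quantitative brain MRI |
| Primary Outcomes | Eight toolbox tests (including language and processing speed), Montreal Cognitive Assessment, episodic memory composite | Connectivity and DTI, plus volumes that are also called primary |
| Statistical Analysis | Cognitive measures, not itemised | Neuroimaging measures, not itemised |

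**The concern.** A paired test in the HIIT arm asks whether scores moved between two dates. They can move because of chemotherapy, familiarity with repeated tests, or time, and all of these act in the control arm too. Randomisation protects only the contrast between arms. A hypothesis partly framed against baseline, with a paired P value attached, invites the reader to treat an uninformative result as support for HIIT.

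The wording of the conclusion adds to this. The stated aim is an effect size for the next trial. A conclusion about efficacy needs a defined test on a defined outcome, and the article gives several tests on many outcomes, each at P<.05, under lists that differ. What is at stake is how the results may be described, and whether the estimate passed to the confirmatory trial is understood as an estimate.

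**Working it through.** **Inputs from the article.** 50 enrolled, 20% dropout, 20 analysed per arm, two-sided alpha .05, no multiplicity adjustment. The equal change in both arms, the correlation between measures and the number of measures counted are assumptions, shown as ranges.

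**1. The plan's own figures.**
- Within-group half-width: t(0.975, 19)/√20 = 2.093/4.472 = 0.47 SD.
- Between-group half-width: t(0.975, 38) × √(2/20) = 2.024 × 0.316 = 0.64 SD.
- Power at 0.91 SD, noncentral t with 38 df and noncentrality 0.91 × √10 = 2.88: 80%.

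All three agree with the Sample Size Calculation. The sample size arithmetic is sound.

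**2. Paired test in the HIIT arm when HIIT does nothing.** Let both arms change by the same δ, in SDs of the change score. The probability p that one paired test is significant comes from the noncentral t with 19 df and noncentrality δ√20. The arms are independent, so the probability that HIIT is significant and control is not equals p(1 − p).

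| δ (assumed) | p | p(1 − p) |
|---|---|---|
| 0.2 | 14% | 12% |
| 0.3 | 25% | 19% |
| 0.46 | 50% | 25% |
| 0.5 | 56% | 25% |
| 0.6 | 72% | 20% |
| 0.8 | 92% | 7% |

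The 25% is a ceiling, since p(1 − p) peaks at p = 0.5. The article gives no value for δ. The table applies to the hypothesis when the common change is an improvement; a common decline would give significant results in the other direction.

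**3. Between-arm tests over several null measures.** For k independent measures, the chance of at least one P<.05 is 1 − 0.95^k in either direction and 1 − 0.975^k in favour of HIIT. Correlated cases were simulated with equicorrelated normal change scores, 20 per arm.

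Two counts of the cognitive measures are defensible:
- k = 10: eight toolbox tests, the Montreal Cognitive Assessment and the composite, as under Primary Outcomes.
- k = 6: only the tests labelled executive function or memory (five) and the composite, which is closer to the Abstract.

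| k | Correlation | Either direction | Favouring HIIT |
|---|---|---|---|
| 10 | 0 | 40% | 22% |
| 10 | 0.3 | 35% | 18% |
| 10 | 0.5 | 29% | 15% |
| 6 | 0 | 26% | 14% |
| 6 | 0.3 | 24% | 12% |
| 6 | 0.5 | 21% | 11% |

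Imaging measures would raise these figures, but the article does not say how many there are.

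**4. Aim against claim.** "the primary objective of the analysis for this pilot study is not to detect a between-group difference but to estimate the effect size" stands in the Sample Size Calculation. The Abstract makes an efficacy conclusion conditional on a positive result that no section defines, and the closing Conclusions drop the condition.

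**The case against.** The strongest reply is that the article contains no rule making a paired P value, or one P<.05 among many, a positive trial. Statistical Analysis opens by tying the analyses to HIIT–control comparisons, and the hypothesis can be read as requiring both contrasts. A success rule may also sit in the full protocol or the analysis plan, which are not shown. This stands. A reader might infer that any single significant result declares success, but the text does not say so. What remains is that the efficacy wording does not exclude that use.

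A reader might also infer that a positive result is likely without any HIIT effect. For the between-arm contrast it is not: favourable false positives run from 11% to 22% in the cases above. Figures above one half arise only for the within-arm test, and only at the larger assumed changes.

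A further tempting step is that the pilot will hand on an inflated effect size. At an assumed true difference of 0.4 SD, power is 23% and significant estimates average about 0.84 SD. That matters only if significant estimates alone are carried forward. The plan describes no such filter, and it reports 95% CIs.

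Finally, not adjusting for multiplicity is disclosed and defensible in a pilot, an estimation study may report several outcomes, and both efficacy statements defer to later trials for confirmation. These points are fair. Non-adjustment is not the fault here, and there is no need to insist on exactly one cognitive and one imaging outcome.

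**Conclusion.** The point holds as a mismatch between aim, tests and claim.

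- The within-arm paired tests on primary variables, and the baseline comparator in the hypotheses, cannot support a HIIT effect. With 20 per arm and equal improvement in both arms, the HIIT test is significant 14% to 92% of the time over an assumed 0.2 to 0.8 SD, and alone significant 7% to 25% of the time.
- The efficacy wording conflicts with the stated estimation aim and rests on primary lists that differ between sections. Under no effect, at least one cognitive measure favours HIIT at P<.05 with probability about 15–22% (10 measures) or 11–14% (6 measures), for correlations from 0.5 to 0. In either direction the figures are 29–40% and 21–26%.

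The sizes rest on the assumed common change, correlations and counts. The logical point about within-arm tests does not depend on them. The between-arm analyses and the sample size figures are unaffected.

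**What to change.** 1. In Statistical Analysis, report within-arm change as means with 95% CIs and drop the paired P values.
2. In Objectives, remove the comparison with baseline, so that the hypotheses rest on HIIT versus attention control.
3. Give one identical primary outcome list in the Abstract, Objectives, Primary Outcomes and Statistical Analysis, stating which toolbox tests, which imaging measures and whether volumes belong to it.
4. In the Abstract and the closing Conclusions, replace the efficacy claim with a statement that the trial estimates the between-arm effect and its CI in order to design a confirmatory trial, and that estimates are carried forward whether or not they are significant.

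The cost is wording, fewer P values and a more modest claim. No change to sample size, visits or data collection is needed. The article reports four patients enrolled by May 2022, so on that record the change could precede most outcome data.

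### Groups are compared by an unadjusted t test on change and an ANCOVA that adjusts for a post-randomization switch; neither leads, and no clean baseline-adjusted intention-to-treat estimate is specified

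*Protocol article*

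**What the plan says.** All of this is in the protocol article.

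- Statistical Analysis sets the outcome variable: "The primary analysis variables will be changed from baseline to week 16 of neuroimaging and cognitive function measures".
- It then gives the between-arm method: "For between-group comparison, a 2-sample *t* test will be performed".
- A second method follows: "Analysis of covariance will also be used to assess the intervention effect on those continuous outcomes (changes from baseline to week 16". Its covariates are described as "adjusting for patient baseline characteristics and other clinical covariates, including any participant who is required to switch to MIIT".
- The next sentence of that section keeps patients who move to MIIT in the HIIT arm for the primary analysis, by intention to treat. It does not say whether that primary analysis is the t test or the ANCOVA. Linear mixed models are also planned to assess group differences.
- Sample Size Calculation states the purpose: "the primary objective of the analysis for this pilot study is not to detect a between-group difference but to estimate the effect size". It enrolls 25 per group, expects 20 per group to be analysable, and quotes the precision as "mean differences between groups with a 95% CI of –0.64 to +0.64 SD units".

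**The concern.** When the outcome is measured before and after treatment, a t test on change fixes the coefficient of the baseline value at 1. ANCOVA estimates that coefficient, which removes more residual variance unless the two measurements are almost perfectly correlated. Here the baseline cognitive and MRI measures are already scheduled (Table 1), so the extra precision needs no new data.

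Three things are at stake:

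- **Precision.** The pilot exists to supply an effect size for the next trial, and its interval may be wider than it needs to be.
- **Chance imbalance.** With about 20 per arm, a baseline difference on any one measure can be sizeable, and the change-score contrast carries part of it into the estimate.
- **No lead estimate.** Each cognitive and MRI outcome gets more than one between-arm result, with no stated order. The ANCOVA as worded is not a ready substitute for the t test, because adjusting for the MIIT switch alters what the arm coefficient measures.

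**Working it through.** **Inputs.** From Sample Size Calculation: 20 analysable per group, since 50 × (1 − 0.20) = 40; half-widths of 0.47 SD (within group) and 0.64 SD (between groups); detectable difference of 0.91 SD at 80% power, two-sided 0.05. Assumed, because the article gives no value: ρ, the correlation of an outcome's baseline and post-intervention values, shown from 0.3 to 0.9. Also assumed: equal variance at both times and in both arms, and a linear relation.

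**Step 1: reproduce the stated figures.**
- Within group: t(0.975, 19)/√20 = 0.468 (stated 0.47).
- Between groups: t(0.975, 38) × √(2/20) = 0.640 (stated 0.64).
- Power at 0.91 SD by the noncentral t with 38 df: 80.1%. Detectable difference at 80% power: 0.909 SD.

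The sizing is correct, and it is that of an unadjusted two-sample t test.

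**Step 2: baseline-adjusted ANCOVA with the same 20 per group.** With outcome variance σ², a change score has variance 2(1 − ρ)σ². The residual after adjustment for baseline has variance (1 − ρ²)σ². The ratio is (1 + ρ)/2. Estimating the slope costs one degree of freedom (37 left) and inflates the standard error by about √(1 + 1/36) = 1.014. In units of the SD of change:

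half-width = t(0.975, 37) × √(2/20) × √((1 + ρ)/2) × √(1 + 1/36)

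| ρ (assumed) | Half-width | Detectable difference, 80% power | Power at 0.91 SD |
|---|---|---|---|
| t test on change | 0.64 | 0.91 | 80% |
| 0.3 | 0.52 | 0.74 | 93% |
| 0.5 | 0.56 | 0.80 | 89% |
| 0.6 | 0.58 | 0.83 | 87% |
| 0.7 | 0.60 | 0.85 | 85% |
| 0.8 | 0.62 | 0.88 | 83% |
| 0.9 | 0.63 | 0.90 | 81% |

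With the penalty included, 20 per group under ANCOVA is worth 20/[((1 + ρ)/2) × (1 + 1/36)] per group under the t test: 25.9 at ρ = 0.5, 24.3 at 0.6, 22.9 at 0.7, 21.6 at 0.8 and 20.5 at 0.9.

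**Step 3: chance imbalance.** The standard error of a baseline mean difference is √(2/20) = 0.32 SD, so about one outcome in three would show a larger difference in either direction (normal approximation). Given a baseline difference d, the change-score contrast shifts by −(1 − ρ)d. At ρ = 0.5 and d = 0.32 the shift is 0.16 SD in size. It averages to zero over randomizations, but not in the one trial that is run.

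**Step 4: the MIIT covariate.** Leave out other covariates and write change = a + b·arm + c·switch. The switch is 0 for every control patient up to week 16. Then b compares HIIT patients who did not switch with controls. The intention-to-treat difference is b + p·c, where p is the share of the HIIT arm that switches. The two agree only if p or c is zero. The article gives neither, so the gap cannot be sized.

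**The case against.** The strongest reply is that nothing here is an error. Under 1:1 randomization the t test on change is unbiased and its interval is valid, and the sample size was worked out for that same test. An ANCOVA is planned as well. Its baseline characteristics may be meant to include the outcome's baseline value, and a journal article may fairly leave the covariate list to a fuller document.

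Most of this stands, and it limits the point:

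- A reader might infer that the t test is biased or that the sample size is wrong. Neither follows: Step 1 reproduces every stated figure.
- A reader might infer that the trial ignores baseline adjustment. It does not; the weakness is the unranked place and the content of the planned ANCOVA.
- A reader might infer a saving of about a quarter of the variance on every primary outcome. The article gives no ρ. At 0.8 to 0.9 the half-width hardly moves, and some imaging measures, such as brain volumes, may lie there.
- A reader might infer that the estimate will be picked after the results are seen. The text leaves room for that but does not show it. The word "also" and the sizing suggest that the t test leads, but the article does not say so.

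What the reply does not answer is the MIIT term. The article does state that covariate, so it is not an omitted detail. The phrase could be read loosely as saying only that such patients stay in the model, but as worded it sits in the list of adjustments. Promoting the ANCOVA as it stands would therefore not give a clean intention-to-treat estimate.

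**Conclusion.** The point holds as a matter of efficiency and clear specification, not validity. The article sets out a valid but less precise between-arm comparison, and beside it an adjusted one whose arm coefficient departs from the intention-to-treat contrast if the MIIT covariate is used as worded. It does not say which leads.

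The loss of precision is moderate for measures with ρ of about 0.3 to 0.7 (half-width 0.52 to 0.60 against 0.64 SD of change), small at 0.8 and negligible at 0.9. These figures rest on the assumed ρ, equal variances, linearity and 20 complete patients per arm. The sensitivity to chance imbalance follows from the arm size and shrinks as ρ rises. The effect of the MIIT term cannot be sized from the article.

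**What to change.** In Statistical Analysis, name one primary between-group estimate for each cognitive and MRI outcome: an intention-to-treat ANCOVA of the post-intervention value (or of change, which gives the same arm coefficient) on arm plus that outcome's own baseline value. State explicitly that the MIIT switch is not a covariate in this model; the existing exploratory analysis of patients who transfer can stay separate. Report the adjusted mean difference with its 95% CI and the residual SD, which the confirmatory trial will need for its sizing. Keep the t test on change as supportive, and say that the mixed models do not replace the primary estimate.

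The stated 0.64 and 0.91 SD can remain as the unadjusted reference figures. The cost is a few sentences and one degree of freedom per model. No new data or visits are needed.
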